The main objective of our study is to answer the question whether it is more (cost) effective to refer for specialised PFMT or for TVT(O) surgery after the standard initial instruction and training given by the GP has failed.

Primary surgery in this group of patients may be cost-effective when compared to PFMT as its cure rate is higher. A comparison of both strategies has been performed in a small sample of patients comparing abdominal Burch surgical procedure versus PFMT.[11] Although this single study concluded that primary surgery was preferable, the design and power did not meet the standards to provide sufficient scientific evidence. Finally, it is unclear which factors are associated with success or failure of PFMT and TVT. After identification of these factors a prediction model can be built that can further individualize treatment. In addition to our cost-effectiveness analyses we aim to develop such a prediction model.

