### Sample size considerations

Literature shows a subjective improvement of incontinence after PFMT up to 65%, and a subjective improvement after TVT(O) of at least 80%. In order to detect this difference with a power of 0.9 and an alpha of 0.05, we need 200 women in each trial arm. For our primary outcome parameter, total cure of incontinence, the expected difference between both arms is much larger: 28% cure after PFMT, and 65% cure after TVT. The 200 women in each treatment arm will be largely sufficient to assess a statistically significant difference in this secondary outcome.

Sample size calculation for the prediction models is based on the number of successes (or failures). For each predictor in the model we need 10-15 successes. Our pre-defined prediction model consists of 5 predictors and the interaction terms with treatment. Our total sample size will exist of 400 women. The expected number of successes (cure) of the PFMT group is 30 (15% of 200) women, the number of women cured after TVT is an estimated 130 (65% of 200 women). So the total number of complete cure is an estimated 160 women, with 240 women being not completely cured. These figures are sufficient for modelling up to 10-12 predefined possible predictors of cure. With respect to subjective improvement an estimated total of 290 women will show subjective improvement as measured with the Patient Global Impression of Improvement (PGI-I) questionnaire (65% of 200 women with PFMT plus 80% of 200 women in TVT group). Thus, 110 women can be considered failures. Again, this also allows us to make a prediction model for improvement with the predefined predictors. Therefore the study sample will also be amply sufficient for prediction purposes.

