### Statistical analysis

Data will be presented as numbers (percentage) for nominal variables or means (standard deviation) for interval variables. Differences between the two interventions will be analysed based on intention-to-treat analysis. For interval variables, differences between the two groups will be analysed with a Students t-test, proportions will be compared using the Chi-square test.

Multivariate logistic regression analysis will be used for the development of the prediction of successful treatment only. In literature, a wide range of patient characteristics were considered to be associated with the outcome of PFMT. In the Consultation on Incontinence (ICI) proceedings it was concluded that there are no reliable factors identified yet, because the number of observations and studies is too low.[2] However, several factors have been identified as possible predictors of a successful outcome after PFMT. To provide information on treatment effectiveness in different subgroups of patients participating in this trial, we will derive a prediction model and estimate interaction of treatment effect with baseline incontinence severity (number of leaks/week), duration of symptoms, increasing parity, Body Mass Index, baseline pelvic floor contraction ability, and treatment modality as factors.[2] The defined prediction model will therefore be pre-specified resulting in less over-optimism than models in which the choice of predictors is strongly driven by the data-set and the need for external validation.[19] From the multivariate logistic model, in which success will be defined as cure (no objective or subjective incontinence) at 12 and 18 months follow-up, we will estimate the weight of the different coefficients. The modelling process will be internally validated by bootstrap resampling. This technique gives an impression of how "over-optimistic" the model is i.e., how much the performance of the model may deteriorate when applied to a new group of similar patients.[20]

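### The prediction model is meant for choosing treatment for individual women, but the validation described looks at pooled performance, which mostly reflects the main effect of treatment

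*Protocol article*

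**What the plan says.** The Background of the protocol article gives the model's purpose: "After identification of these factors a prediction model can be built that can further individualize treatment". The Abstract likewise says that treatment strategy and patient characteristics will be combined to guide choices for individual future patients.

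Under Patient outcome measures, the model is the fifth secondary outcome, and the therapy given enters as an independent variable. Sample size considerations and Statistical analysis describe five baseline predictors (severity, symptom duration, parity, body mass index and pelvic floor contraction ability) and their interactions with treatment. Statistical analysis defines success as cure, both objective and subjective, at 12 and 18 months.

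The same section says that the modelling process will be validated internally by bootstrap resampling, to show "how much the performance of the model may deteriorate when applied to a new group of similar patients". It describes no other validation.

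Sample size considerations supplies the expected cure rates. The paragraph on the trial size has "28% cure after PFMT, and 65% cure after TVT". The paragraph on the model has "The expected number of successes (cure) of the PFMT group is 30 (15% of 200) women", keeps 65% for TVT, and concludes "So the total number of complete cure is an estimated 160 women, with 240 women being not completely cured".

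**The concern.** Choosing between two treatments for one woman needs her predicted difference in cure between TVT and PFMT. The overall performance of a pooled model is a different quantity. It measures how well the model separates cured from uncured women across both arms together. Treatment is in the model and its expected effect is very large, so much of that separation comes simply from knowing which arm a woman was in. That does not help to tell one woman's benefit from another's.

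Bootstrap correction removes overfitting but keeps the genuine main effect of treatment. Good corrected performance is therefore compatible with a model that holds no information on who benefits from which treatment. At stake is how the result is read: a favourable pooled figure could be taken as support for individual treatment choice when it mostly repeats the trial's main comparison.

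**Working it through.** **Inputs**, all from Sample size considerations: 200 women per arm; cure after PFMT 15% (model paragraph) or 28% (trial-size paragraph); cure after TVT 65%; subjective improvement 65% v 80%.

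**The plan's own figures.** Cured: 0.15 × 200 + 0.65 × 200 = 30 + 130 = 160. Not cured: 400 − 160 = 240. Improved: 130 + 160 = 290; failures 400 − 290 = 110. All reproduce.

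**c-statistic of treatment alone.** Take every pair of one cured and one uncured woman. A pair counts 1 if only the cured woman had TVT, one half if both were in the same arm, and 0 otherwise.

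- Cure, 15% v 65% (PFMT 30 cured, 170 not; TVT 130 cured, 70 not): [130 × 170 + 0.5 × (130 × 70 + 30 × 170)] / (160 × 240) = 29,200 / 38,400 = 0.760.
- Cure, 28% v 65% (PFMT 56 cured, 144 not): [130 × 144 + 0.5 × (130 × 70 + 56 × 144)] / (186 × 214) = 27,302 / 39,804 = 0.686.
- Improvement, 65% v 80% (PFMT 130 improved, 70 not; TVT 160 improved, 40 not): [160 × 70 + 0.5 × (160 × 40 + 130 × 70)] / (290 × 110) = 18,950 / 31,900 = 0.594.

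**What bootstrap correction would show if no predictor worked.** The simulation used 150 trials of 400 women for each pair of cure rates. It had five independent normal predictors unrelated to cure, and a logistic model with treatment, the five predictors and five interactions. Optimism was estimated from 60 bootstrap resamples per trial. Calibration slopes and the interaction test come from a second set of 150 trials of the same design.

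| Mean over trials | 15% v 65% | 28% v 65% |
|---|---|---|
| Treatment-only c (from above) | 0.760 | 0.686 |
| Pooled c, apparent | 0.796 | 0.725 |
| Pooled c, corrected | 0.769 | 0.693 |
| Bootstrap calibration slope, pooled | 0.89 | 0.84 |
| Within-arm c, apparent (PFMT / TVT) | 0.62 / 0.58 | 0.60 / 0.59 |
| Within-arm c, corrected (PFMT / TVT) | 0.54 / 0.52 | 0.53 / 0.53 |
| Joint 5-df interaction test, p < 0.05 | 4% | 4.7% |

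Pooled c falls by only 0.796 − 0.769 = 0.027 and 0.725 − 0.693 = 0.032. Both corrected values look respectable, and the pooled calibration slope does not reveal the problem either. Three summaries do show that the model has no individual content: within-arm c near chance, a gain over treatment alone of only 0.769 − 0.760 = 0.009 and 0.693 − 0.686 = 0.007, and an interaction test that rejects at about its nominal rate.

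**The case against.** The strongest defence is that the quoted sentence is accurate: the bootstrap does estimate how over-optimistic a model is, and the article claims no more for it. That stands. A reader might infer that the protocol treats bootstrap performance as proof of individualisation. It does not say so, and it sets no threshold for calling the model validated.

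A reader might also infer that this part of the trial could not fail, or that an empty model would necessarily pass as validated. The article does not support that either. It separately commits to estimating the interactions of treatment with the five baseline factors, and those estimates address whether benefit differs between women. In the noise simulation a joint test of them rejected at about its nominal rate, so a null result could be seen from terms that the plan already includes. What remains is that the one validation step described is not directed at them.

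It is also fair that the article never names the c-statistic, and that the choice of measure may sit in an analysis plan that is not shown. The unnamed measure is therefore not the point. The point is the stated target, overall performance of a pooled model, set against the stated purpose.

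Two limits on size also stand. The noise simulation is an extreme case, because the article regards several of the factors as possible predictors. And in that simulation the fitted model predicted PFMT to be better on cure for well under 1% of women, so it does not show women being steered to the wrong arm. It shows only that pooled performance cannot tell whether predicted differences in benefit are real.

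**Conclusion.** The concern holds in this limited form: the described validation does not test the use for which the model is intended. On the article's cure rates treatment alone yields c = 0.76 or 0.69. The two values arise because the article gives two PFMT cure rates. With useless predictors, corrected pooled performance stays at 0.77 or 0.69 while corrected within-arm discrimination is about 0.53.

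The treatment-only figures need nothing beyond the article's rates and equal arms of 200. The simulation figures assume independent normal noise predictors and take pooled c and calibration slope as examples of performance. The point is strong for cure and weaker for subjective improvement, which Sample size considerations also foresees modelling and where treatment alone gives only 0.59. The primary comparison and the trial size are unaffected. This is a worthwhile, inexpensive improvement to a secondary aim.

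**What to change.** Keep the pre-specified model and the bootstrap. From the same resamples, also report:

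- optimism-corrected discrimination and calibration within each arm;
- the gain over a treatment-only model and over a model with main effects but no interactions;
- calibration of the predicted TVT-minus-PFMT cure difference, for example observed against predicted difference by quarters of predicted benefit.

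Add a joint likelihood-ratio test of the five treatment interactions, and state that any conclusion about individualising treatment will rest on these results rather than on pooled performance.

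The cost is analysis-plan wording and a few extra summaries; no new data or visits are needed. There are two downsides. The reported performance will look less favourable. Benefit calibration will also be imprecise with 400 women: a quarter holds about 50 women per arm, so at 15% v 65% the standard error of the observed difference is √(0.15 × 0.85/50 + 0.65 × 0.35/50) = 0.084, a 95% interval of about ±17 percentage points (1.96 × 0.084 = 0.165). It should be presented with its uncertainty.

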### Time plan

Patient recruitment started in March 2008 and is planned to continue until December 2009. The follow-up period is 18 months, and therefore will continue until June 2011. The study is conducted in cooperation with the urogynaecology consortium of the Netherlands. Most participating clinics have disposition over a research nurse for follow-up and data collection in order to fill out the web-based case record forms.

### Knowledge transfer

Outcome of the PORTRET trial will be important for reconsidering the added value of prescribing PFMT to every patient with stress-incontinence as primary treatment, as well as comparing objective and subjective treatment success or failure between TVT and PFMT. The results of this study will be submitted to different international and national scientific associations such as the International Continence Society (ICS).
